#### Treatment satisfaction and presence

The presence in VR was assessed using Igroup presence questionnaire (IPQ). This is a 14 items questionnaire assessing different aspects of presence and immersion into VR world through items such as: “In the computer generated world I had a sense of being there” or “How aware were you of the real world surrounding while navigating in the virtual world? (i.e. sounds, room temperature, other people, etc.)?”. In the end, once the IPQ completed, the patients will be instructed to answer an additional question (i.e., are you willing to use VR systems in the future?) with dichotomous response developed by the authors for assessing the willingness for further sessions with VR system.

#### Opioids used

The amount of analgesic used will be extracted from the medical records. The usage of opioids will be coded as present and absent. The mean drug metabolism time will be calculated in order to determine if an opioid agent is active, coding 1 if the opioid agent is active and 0 if is out of his action range.

#### Pain catastrophizing

Level of catastrophizing was measured through the Pain Catastrophizing Scale (PCS) [52]. This scale is a self-report measure with 13 items structured in three subscales, namely rumination, magnification, and helplessness, and proved good psychometrics properties. Patients were instructed to answer on a scale from 0 (“not at all”) to 4 (“all the time”).

#### Assessment of mood

Anxiety and depression levels were assessed through the Hospital Anxiety and Depression Scale (HADS) [53]. This scale is a self-report measure with 14 items, with half of the items measuring anxiety symptoms (e.g., items targeting tension, panic attacks) and the other half measuring depression symptoms (e.g., items targeting anhedonia or inability to enjoy things or experiences). Responses are recorded on a scale from 0 to 3, and each item has a different response in accordance with the item content.

#### Cognitive abilities

Cognitive abilities were measured through the Six-item Cognitive Impairment Test (6CIT) [54], a screening tool for measuring the global cognitive status. The items of the 6CIT cover six questions: one assessing the memory (remembering a 5-item name and address), two items including calculation (reciting numbers backward from 20 to 1 and months of the year backward), and three items assessing orientation (year, month, and time of day). The cutoff of seven from the total score was used for excluding patients with low cognitive abilities [55].

### Statistical analysis

#### Preliminary analyses and preprocessing data of skin conductance

Demographic characteristics and psychological measures will be explored for missing data, and distribution abnormalities. Means and standard deviations will be used to characterize the sample. Preprocessing of skin conductance measure will be performed using AcqKnowledge 4.1 first through the visual inspection of the raw signal, and then applying the smoothing function with a smoothing factor of three samples. This function has the same effect as the low pass filter by replacing the high-frequency signal with the mean values across three milliseconds to subtract the artifacts, without changing the wave form.

#### Main analyses

Behavioral data will be analyzed using STATA 16.1 in accordance with the intent to treat principal [56]. Descriptive statistics (i.e., age, gender, assessment of mood, pain catastrophizing, opioid consumption, level of pain intensity, level of relaxation) for the baseline values will be presented within each randomized group. These will include counts and percentages for binary variables and mean and standard deviations, or medians with lower and upper quartiles, for continuous variables, along with minimum and maximum values and missing values. There will be no tests of statistical significance or confidence intervals for differences between randomized groups on any baseline variable. The effectiveness of the intervention on pain intensity (primary outcome) will be assessed by employing random coefficient analysis. We will include the time of assessment, group assignment (VR intervention and standard of care), and the interaction between time of assessment and group in the multi-level regression model. Similarly, for the secondary outcome’s measures (relaxation, time spent by patients thinking about pain, and treatment satisfaction and presence) random coefficient analysis will be performed. Although the intervention is minimally invasive, the adverse effects of the VR intervention will be measured with SSQ scale and pre-post differences will be assessed by *t*-test statistic or the non-parametric equivalent. Physiological data will be processed using the AcqKnowledge 4.1 software, and for each patient, a difference score in the area under the curve between the last 5 min of measurement and baseline level of SC will be extracted. Pearson correlation will be employed to examine the relationship between the level of SC and pain intensity (as a difference score between pre-post intervention). A *P* value will be used to estimate statistical significance for all analyses.

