### Study sample size

Using G*Power 3.1.9.2 [39], we had estimated a minimum of 50 participants (25 in each group) needed to detect an effect size of 0.49, with *α* = 0.05 and power = 0.80. The expected effect size of 0.49 was chosen in the light of the results found by the most recent meta-analyses [25, 26], being a conservative effect size given that in their analysis Chan and colleagues [25] found a medium effect size (SMD = − 0.49, 95% CI − 0.83 to − 0.14) and the analysis of Georgescu and colleagues [26] a large effect size was found (Hedges’*g* = 1.08, 95% CI 0.46 to 1.70) for studies with parallel design aiming to decrease pain at hospitalized patients. However, as we expected some dropouts (based on other studies using VR systems for treating anxiety [40]) and some incomplete or unusable data, especially on the physiological measure, we aim to recruit 30 participants in each group.

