### Outcomes

The present study assesses the efficacy of a Nature Track© VR to decrease pain intensity in surgical patients. The primary outcome is pain intensity measured right before the exposure to the VR content and after. The secondary outcomes measure the effects of the application on relaxation and the amount of time spent by each patient thinking about pain. Also, the primary outcome was complemented with measures of the adverse effects, level of immersion, and level of presence in the VR.

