## Measures

### Primary measures

#### Pain

The pain intensity was measured using the Numerical Rating Scale (NRS) [41] by asking participants to report their intensity before and after the intervention on a scale from 0 (“no pain”) to 10 (“extremely painful”). To help patients to discriminate between different pain levels, they were asked to report the mean level of pain intensity in the last 24 h, the peak of intensity in the same period, and the intensity right before the intervention. We chose NRS for this study rather than other measures more extensively used, such as visual analog scales (VAS), due to the consensus of the better psychometrics properties [42–45]. The value of pain right before the intervention will be used in the analysis of VR effectiveness.

Concomitantly, as a physiological indicator of postoperative pain were measured the fluctuations of the SC [46–48]. The SC were measured using the BIOPAC MP150 system (Biopac Systems, CA,USA). The two finger electrodes were attached to the first phalange of the index and medius fingers from the non-dominant hand with Velcro straps. The electrodes were connected to the computer using the USB connection input. To ensure good contact with the skin, isotonic gel was added to the electrodes prior to attaching to the fingers. At the beginning, participants had few minutes to relax, get ready and comfortable with the experimental environment. After that, patients were instructed not to move for the duration of the recording.

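### The planned time-by-group test on two pain ratings is valid, but a baseline-adjusted model would be more precise at almost no cost

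*Protocol article*

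**What the plan says.** The Outcomes section defines the endpoint: "The primary outcome is pain intensity measured right before the exposure to the VR content and after". The Pain section asks for several ratings beforehand (the 24-hour mean, the 24-hour peak and the current level) and then chooses one: "The value of pain right before the intervention will be used in the analysis of VR effectiveness". Each patient therefore contributes two ratings to the primary analysis.

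The Main analyses section names the method: "The effectiveness of the intervention on pain intensity (primary outcome) will be assessed by employing random coefficient analysis". It then gives the terms: "We will include the time of assessment, group assignment (VR intervention and standard of care), and the interaction between time of assessment and group". It mentions no baseline covariate, no term for type of surgery, no random slope and no covariance structure. Relaxation, also rated before and after, gets the same analysis. The Randomization and blinding section says that randomisation was done within type of surgery.

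**The concern.** There are two questions. The first is whether the named model suits two occasions. A random coefficient model usually lets the time effect vary between patients, and two ratings per patient carry too little information to separate that variation from residual error unless something is restricted.

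The second matters more: what the time-by-group term estimates. The listed terms leave the baseline means free to differ between arms, although randomisation makes them equal in expectation. The contrast is then a comparison of change scores, which subtracts the baseline in full instead of weighting it by how well it predicts the later rating. At stake is precision in a small trial. The Trial status section reports that recruitment has ended, so the choice of analysis is one of the few ways left to gain precision.

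**Working it through.** **Inputs.** Two occasions (Outcomes; Pain). Effect "needed to detect an effect size of 0.49, with" alpha and power given as "0.05 and power = 0.80" (Study sample size). Stated minimum: "we had estimated a minimum of 50 participants (25 in each group". Target: "we aim to recruit 30 participants in each group". Assumed, because the document does not give them: the pre-post correlation r (shown from 0.3 to 0.8), equal variances before and after, a 0.49 SD difference at the post-session rating with none at baseline, two-sided alpha, and complete data.

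**The plan's own figure.** A two-sample t-test at 0.49 SD needs 67 per group two-sided (53 one-sided), not 25. Power is 0.40 at 25 per group and 0.46 at 30, two-sided. For the planned interaction under the effect assumed here (Cohen's f = 0.49/4 = 0.1225), a total of 50 is reached only if r is about 0.82. If f is taken as 0.49/2 = 0.245, it is reached at r of about 0.27 to 0.29. The document states no r. The sample size is a separate matter and is background here.

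**Step 1: identifiability.** Code time as 0 and 1. Let s00, s11 and s01 be the intercept variance, slope variance and their covariance, and e the residual variance. Then:
- Var(pre) = s00 + e
- Cov(pre, post) = s00 + s01
- Var(post) = s00 + 2·s01 + s11 + e

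That is four parameters on three moments (rank 3 of 4), so the unrestricted form is not identified. With s01 = 0 there are three parameters on three moments, which is identified, but Var(post) cannot then be smaller than Var(pre). With a random intercept only there are two parameters, both identified.

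**Step 2: what the interaction estimates.** The fixed effects fit all four group-by-time means, so with complete data the interaction is the difference in mean change. In a simulated complete data set with 30 per group, the random-intercept interaction was -0.8329 (SE 0.4214) and the change-score difference was -0.8329 (SE 0.4214). Adding a random slope left both unchanged to four decimals. ANCOVA on the same data had SE 0.3633.

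**Step 3: efficiency.** With unit variances, the change score has per-patient variance 2(1 - r) and ANCOVA has residual variance 1 - r². The ratio of ANCOVA to change score is (1 - r²)/[2(1 - r)] = (1 + r)/2. The standardised effect is 0.49 divided by the square root of the variance.

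| r | Variance: change / ANCOVA | Ratio (1+r)/2 | Effect: change / ANCOVA | Power at 30 per group: change / ANCOVA | n per group for 80%: change / ANCOVA |
|---|---|---|---|---|---|
| 0.3 | 1.40 / 0.91 | 0.65 | 0.414 / 0.514 | 0.35 / 0.50 | 93 / 61 |
| 0.5 | 1.00 / 0.75 | 0.75 | 0.490 / 0.566 | 0.46 / 0.58 | 67 / 51 |
| 0.7 | 0.60 / 0.51 | 0.85 | 0.633 / 0.686 | 0.67 / 0.74 | 41 / 35 |
| 0.8 | 0.40 / 0.36 | 0.90 | 0.775 / 0.817 | 0.84 / 0.88 | 28 / 25 |

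Below r = 0.5 the change score has variance above 1, so it is less precise than the post rating alone (0.35 against 0.46 at r = 0.3).

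**Step 4: simulation, 4,000 replicates, 30 per group, r = 0.3, 0.5, 0.7.** Type I error was 0.041 to 0.049 for the change score and 0.043 to 0.050 for ANCOVA. Power was 0.35 against 0.49, 0.46 against 0.57, and 0.67 against 0.73, in line with the table.

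**The case against.** A reader might infer that the primary model cannot be fitted to two time points. The document does not support this. It never specifies a random slope, and the random-effects structure is the kind of detail an article may leave to a fuller plan. A random-intercept model with the listed terms is a proper two-occasion model. Even where the unrestricted slope model fails, the failure lies in the variance components, and in the check the treatment estimate and its standard error did not move.

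A reader might also infer that baseline pain is thrown away. It is not: it enters as the first occasion, with its coefficient in effect fixed at 1. Nor is the planned test biased or anti-conservative.

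Two further objections have force. First, the gain depends on an unknown correlation. The two ratings fall within one session, around some 20 minutes of recording, so r could be high, and at 0.8 the gain is only 0.84 to 0.88. Second, ANCOVA drops patients with no post-session rating, whereas a mixed model keeps them; the protocol expects dropouts and promises intention-to-treat analysis. The constrained-baseline model answers the second objection. The first limits the size of the gain but not its direction. With SDs s0 before and s1 after, the change-score variance minus the ANCOVA residual variance is (s0 - r·s1)², which is never negative. Against it stands only the small cost of estimating one slope.

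**Conclusion.** The point holds as a question of efficiency and clarity. The planned interaction is a valid, unbiased change-score comparison when data are complete, and less precise than baseline adjustment. Under the assumptions listed, adjustment cuts the variance by 35% at r = 0.3, 25% at 0.5, 15% at 0.7 and 10% at 0.8, which adds between 0.15 and 0.04 to power at 30 per group. The gain from including type of surgery was not quantified.

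The label for the model is ambiguous about the random effects. One reading, an unrestricted intercept and slope, leaves the variance components unidentified and may cause convergence trouble, without altering the treatment estimate. The shortfall in the stated sample size makes precision more valuable but does not make this test wrong. The change is a free improvement.

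**What to change.** Before the data are analysed, restate the primary analysis as one of the following:

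- **Constrained-baseline repeated-measures model:** a common baseline mean in both arms, an unstructured 2x2 covariance and no random slope. This keeps patients who have only a pre-session rating, which suits the intention-to-treat aim.
- **ANCOVA:** post-session NRS on group and pre-session NRS.

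In either case include type of surgery, within which randomisation was done, and report the adjusted mean difference with its 95% confidence interval. Use the same model for relaxation. It does not carry over to time spent thinking about pain, which is rated only after the session.

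The cost is a change of wording, plus the notice to the ethics committee and the registry update that the Oversight and monitoring section already requires. No new data are needed, because the baseline rating and type of surgery are already recorded. The Trial status section says that analysis had not been performed. If outcome data have since been examined, the change should be reported as made afterwards.

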#### Time spent thinking about pain

Another factor which can contribute to an increased perception of pain intensity is the amount of thinking time spent by a patient at pain [49]. Consequently, we asked patients to report after the interventions, on NRS from 0 (“not at all”) to 10 (“all the time”), the amount of time they spent thinking about their pain during the exposure to the VR content in the experimental group and during the measuring of SC conductance in the control group.

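### The time-by-group random coefficient model is prescribed for secondary outcomes that are measured only once, so it cannot be fitted to them as written

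*Protocol article*

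**What the plan says.** For the primary outcome, Main analyses specifies a multi-level regression: "We will include the time of assessment, group assignment (VR intervention and standard of care), and the interaction between time of assessment and group". The next sentence says that the secondary outcomes will be handled similarly, and lists relaxation, "time spent by patients thinking about pain, and treatment satisfaction and presence) random coefficient analysis will be performed". It makes no exception for any outcome on that list.

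The Secondary measures sections describe how these outcomes are collected.

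- **Time spent thinking about pain:** "we asked patients to report after the interventions, on NRS from 0" to 10. The question refers to the period "during the exposure to the VR content in the experimental group and during the measuring of SC conductance in the control group".
- **Treatment satisfaction and presence:** the instrument is the IPQ. "This is a 14 items questionnaire assessing different aspects of presence and immersion into VR world". After it, at the end, comes one further question on future use of VR, "with dichotomous response developed by the authors for assessing the willingness for further sessions with VR system".
- **Relaxation:** a 0 to 10 rating before and after the session, in both groups.

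Under Randomization and blinding, and again under the control group description, control patients go through the measurements without VR exposure.

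**The concern.** A model with time, group and their interaction needs at least two assessments per patient in both arms. Relaxation has that structure. Time thinking about pain does not: it has one value per patient, and no pre-session value could exist because the question is about the session. Presence has one value per patient and, for unexposed controls, no meaningful content. The item after the IPQ is binary, so the linear form used for pain does not suit it either.

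Two things are at stake. First, the article names a method for these outcomes that conflicts with its own measurement schedule, so the replacement would be chosen with the data already in hand: Trial status says that recruitment is complete and analysis not yet done. Second, a literal reading invites a between-group test of IPQ scores, with a P value, in which any control values would describe an environment those patients never saw.

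**Working it through.** The plan gives no figure to reproduce here. The question is whether each outcome's data can support the prescribed model.

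**Model.** For patient *i* at time *t* (0 = before, 1 = after) in group *g* (0 = control, 1 = VR):

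y = b0 + b1·t + b2·g + b3·(t × g) + u(i) + e(i,t)

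All four fixed effects are estimable only if the design matrix [1, t, g, t × g] has rank 4. The patient effect u(i) can be separated from the residual only with at least two values per patient.

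**Inputs.** The check uses 30 patients per arm, the recruitment target under Study sample size. The ranks do not depend on that number. The measurement schedules come from the Secondary measures and Data collection procedure sections.

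**Pain and relaxation (before and after, both arms).** Rows: 2 arms × 30 × 2 times = 120. Rank 4 of 4, with two values per patient. The fixed effects are estimable.

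**Time thinking about pain (after only, both arms).** Rows: 2 × 30 × 1 = 60. Since t = 1 throughout, the column t equals the intercept and the column t × g equals g. Rank 2 of 4. The model collapses to

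y = (b0 + b1) + (b2 + b3)·g + [u(i) + e(i)]

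Only the group contrast (b2 + b3) can be estimated. The variances of u and e appear only as their sum.

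**IPQ and willingness (after only).** Two readings are possible.

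- *VR arm only:* 30 rows with t = 1 and g = 1 throughout. All four columns are identical, so the rank is 1 of 4. Not even a group contrast exists.
- *Both arms:* 60 rows, rank 2 of 4, as for time thinking about pain. A group contrast exists arithmetically, but for the IPQ it sets a presence score against answers about an environment not experienced.

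| Outcome | Rows | Rank (4 needed) | Values per patient |
|---|---|---|---|
| Pain, relaxation | 120 | 4 | 2 |
| Time thinking about pain | 60 | 2 | 1 |
| IPQ, willingness, VR arm only | 30 | 1 | 1 |
| IPQ, willingness, both arms | 60 | 2 | 1 |

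**After the change.** With the time terms removed, time thinking about pain supports intercept plus group: rank 2 of 2 on 60 rows. Adjusting for surgery type (three types, so two indicators) and baseline pain makes 1 + 1 + 2 + 1 = 5 coefficients. With complete data that leaves 60 − 5 = 55 residual degrees of freedom.

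**The case against.** The best defence is that the carry-over to secondary outcomes is loose drafting. For time thinking about pain the fallback is nearly forced: drop the time terms and the random effect, and a group comparison remains. That stands, and it limits the analyst's freedom. It does not rescue the text, which repeats the method by name, and no random coefficient model fits one value per patient. Nor is this detail that an article may leave to an analysis plan, because the article itself fixes the method.

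Several stronger readings are tempting, and the document does not support them.

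- *No secondary measure except relaxation can support a time effect.* The simulator sickness questionnaire also stands under Secondary measures and is completed before and after. It has its own pre-post test and was never assigned to this model.
- *Presence and willingness were collected only in the VR arm.* This is an inference. The control group description says in general terms that controls followed the same protocol for psychological measures, and the assessment overview (Fig. 2) is not shown. Presence is mentioned in the VR-arm description, but in the same sentence as catastrophizing and mood, which are to be reported for both groups. For the IPQ the inference is strong from its content. For willingness it is weaker, since an unexposed patient could answer.
- *The plan names willingness as an outcome for this model.* It names treatment satisfaction and presence. Willingness is tied to that phrase only through the heading under which the item is described.

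**Conclusion.** The point holds for the outcomes assigned to this model other than relaxation. For time thinking about pain it rests on explicit text: the time effect, the interaction and the patient-level random effect cannot be estimated (rank 2 of 4), while the group contrast can be recovered. For the IPQ and willingness it rests on their being single end-of-session measures. On either reading of who completed them, the time terms are inestimable (rank 1 or 2 of 4), and the IPQ has no meaningful comparator.

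The reach is limited. The Outcomes section names two secondary outcomes, relaxation and time thinking about pain, and one of the two is affected; presence is there only as a complement to the primary outcome. A reader might infer that the trial's main result is compromised. It is not: pain is rated before and after in both arms, and this point leaves its model untouched. The text should be corrected before analysis, but the defect does not rank with those that endanger the primary conclusion.

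**What to change.** Replace the sentence on secondary outcomes with outcome-specific analyses, dated before any analysis:

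1. **Time thinking about pain:** compare the single post-session score between groups by linear regression on group, adjusted for surgery type (the randomisation stratum) and for pain right before the session.
2. **IPQ:** describe it in the VR arm only (mean, SD, 95% CI), with no between-group test.
3. **Willingness:** report the VR-arm proportion with an exact 95% CI.

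The same text should state which arms completed the IPQ and the willingness item. The relaxation model need not change for this reason.

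The cost is a change of wording plus the steps that Oversight and monitoring requires: a report to the ethics committee and an update of the registry entry. No new data are needed. Since Trial status says that analysis had not been performed, the change can still be made as a pre-analysis clarification.

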
## Objectives

The aim of this study is to assess whether exposure to relaxing VR environments is associated with decreased levels of pain after surgery after varicose veins, hernia repair, or gallbladder surgeries. Surgeries of varicose veins, hernia repair, and gallbladder were aggregated due to similarities across (1) the incidence rate [32–34], (2) levels of pain intensity after surgery [35–37], and (3) odds of acute pain to be translated into CPSP [35–37]. We hypothesize that VR-based intervention will have a better result in decreasing pain when it is used as a complementary treatment of standard care compared with the standard care alone. Additionally, we will assess the safety of VR-based intervention in patients after surgery.

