#### Control group: standard of care intervention

Patients allocated to the standard of care group followed the treatment after surgery as prescribed by current medical personnel. In addition, they followed the same protocol as the patients in the intervention group regarding psychological and physiological measures. Specifically, they were conducted in the treatment room and asked to indicate the non-dominant hand for setting up the equipment to SC measures. After that, the SC was measured continuously for 20 min without exposure to the VR environments. At the end, they completed de psychological measures and were conducted in their hospital room.

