#### Adverse effects

Potential adverse effects were evaluated using the Simulator Sickness Questionnaire (SSQ) [50]. As some of the unintended effects of VR could also be effects of the opioid’s consumptions (e.g., headaches, nausea), we have asked participants to complete the scale twice, before and after the exposure of VR. The SSQ was previously validated and proved robust psychometric properties [50, 51] being the most widely measure of cyber-sickness. The patients were instructed to answer on a 4-point Likert scale, corresponding to not at all, slight, moderate, and strong sensations regarding the occurrence of possible side effects such as general discomfort, fatigue, headache, and dizziness.

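### The safety analysis tests pre-post change in the SSQ and names no between-arm comparison, so symptom change shared by both arms could be attributed to VR

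*Protocol article*

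**What the plan says.** The Objectives section of the protocol article adds a safety aim to the efficacy aim: "Additionally, we will assess the safety of VR-based intervention in patients after surgery". No hypothesis or estimand is attached to it.

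The Adverse effects section explains why a baseline was taken. It notes that "some of the unintended effects of VR could also be effects of the opioid’s consumptions", and for that reason "we have asked participants to complete the scale twice, before and after the exposure of VR".

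The only inferential plan for the SSQ is in Main analyses: "the adverse effects of the VR intervention will be measured with SSQ scale and pre-post differences will be assessed by" a t-test or the non-parametric equivalent. The text does not say whether the test is paired or independent, and it mentions no group term.

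The same section treats other outcomes differently. Pain gets a model with time, group and "the interaction between time of assessment and group in the multi-level regression model". Random coefficient analysis is also planned for the listed secondary outcomes, namely "relaxation, time spent by patients thinking about pain, and treatment satisfaction and presence". The SSQ is not in that list.

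On the control arm, the section on standard of care says that "they followed the same protocol as the patients in the intervention group regarding psychological and physiological measures".

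**The concern.** The trial is randomised and its controls spend a comparable period in the same treatment room. Yet its safety aim appears to rest on change within patients. Such a change mixes the effect of VR with whatever else happens to symptoms between the two questionnaires. If symptoms rise for reasons unrelated to VR, the rise would be attributed to VR. If they fall, for example as patients rest, real VR sickness could be hidden. A mean change can also conceal a few patients who become markedly unwell, and anyone who stops early because of sickness may have no post-session SSQ to contribute.

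**Working it through.** **1. Is there a figure to reproduce?** No. The article gives no SSQ mean, SD, expected change or power. The drifts and effects below are therefore assumptions, in units of the SD of the pre-post change.

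**2. What each test estimates.** Let δ be the pre-post drift common to both arms and τ the additional change caused by VR.
- Within the VR arm, the mean change estimates δ + τ.
- The between-arm difference in mean change estimates (δ + τ) − δ = τ.

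Opioid symptoms that are the same at both time points enter neither δ nor τ, because the pre-session score subtracts them. Opioid effects that change during the session do enter δ.

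**3. Inputs.** n = 30 per arm is the recruitment target in Study sample size; n = 25 is the stated minimum there. A two-sided α of 0.05 is assumed, since the article gives 0.05 without sidedness.

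**4. False attribution when τ = 0.** The paired t-test has n − 1 degrees of freedom and noncentrality δ√n. At n = 30, √30 = 5.477.

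| Shared drift δ | Noncentrality, n = 30 | Paired test rejects, n = 30 | Paired test rejects, n = 25 | Between-arm test rejects |
|---|---|---|---|---|
| 0 | 0 | 5.0% | 5.0% | 5% |
| 0.2 | 1.095 | 18.5% | 16.1% | 5% |
| 0.3 | 1.643 | 35.5% | 30.2% | 5% |
| 0.5 | 2.739 | 75.4% | 67.0% | 5% |

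**5. Masking.** With τ = 0.5 and δ = −0.3, the paired test sees 0.5 − 0.3 = 0.2. It rejects 18.5% of the time, against 75.4% with no drift.

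**6. The price of the between-arm test.** For unadjusted change scores the noncentrality is τ√(n/2), with 2n − 2 degrees of freedom. At 30 per arm, √15 = 3.873.

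| VR effect τ | Noncentrality | Power, between arms |
|---|---|---|
| 0.3 | 1.162 | 20.8% |
| 0.5 | 1.936 | 47.8% |
| 0.8 | 3.098 | 86.1% |

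The 95% CI half-width is about 2.002 × √(2/30) = 0.52 SD of change, compared with 2.045 × √(1/30) = 0.37 for the within-arm mean. The wider interval is the honest one for τ, since the narrower one is centred on δ + τ.

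**7. Do control SSQ data exist?** The places in the article do not settle this.
- For: the control section says controls followed the same protocol for psychological measures.
- Silent or against: the treatment-group section lists VR adverse effects among its before-and-after measures; the Adverse effects section times the SSQ around VR exposure; Data collection procedure names only pain intensity and relaxation as taken before and after in both arms; the control section speaks of completing psychological measures at the end.

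**The case against.** The strongest reply is that the article does not rule out a comparison of arms. An independent t-test of pre-post difference scores fits its words, and the choice between paired and independent could be left to an analysis plan that is not shown. This stands as far as it goes: a reader might infer that a between-arm test has been rejected, and the text does not say that. Still, the section names group explicitly for pain and leaves both group and the random coefficient model out for the SSQ, so within-arm is the natural reading. If a comparison of arms was intended, the text should say so.

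Other stronger readings also fail:
- **That the design cannot separate VR sickness from opioid effects at all.** The pre-session SSQ is there to remove stable opioid symptoms and does so. Strong opioids are also an exclusion criterion. Only opioid effects that change over about 20 minutes remain. The planned opioid-active code is not linked to the SSQ analysis.
- **That regression to the mean biases the change.** Nobody was selected on SSQ score, so no mechanism is evident.
- **That a usable control comparison certainly exists.** It is implied, not stated. Recruitment ended in September 2019, so missing control data cannot now be collected.
- **That stops for sickness go unrecorded.** Randomization and blinding counts early stops as dropouts and provides a short interview on the reasons. What is not stated is how these enter the safety results.
- **That the sponsor will read a non-significant result as safety.** The article does not say so. It does rely on P values for all analyses and expects minimal side effects, so a caution is worthwhile.

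It is also fair that no drift of any size is shown for this trial, and that safety is an additional aim for one short session described as low risk.

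**Conclusion.** The point holds in limited form. The article gives its safety aim a pre-post test of the SSQ and states no between-arm comparison, although controls appear to have followed the same psychological measurements. On the natural within-arm reading, the test cannot distinguish VR sickness from session changes common to both arms. Under assumed shared drifts of 0.2 to 0.5 SD of change and no VR effect, the rejection rate at 30 patients rises from 5% to between 18.5% and 75.4%. These figures show how the test behaves; they do not estimate bias in this trial. The conclusion rests on the within-arm reading, and the proposed remedy on control SSQ data existing at both time points. The primary pain analysis is unaffected.

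**What to change.** 1. State whether the SSQ was completed before and after the session in both arms.
2. If it was, make the main SSQ analysis a between-arm comparison: post-session SSQ regressed on group, pre-session SSQ and surgery type (randomisation was done within surgery type), reported as an adjusted difference with a 95% CI. Keep the within-VR change as description only.
3. Tabulate by arm the patients with any SSQ item worsening to moderate or strong, and the stops for sickness taken from the interviews already planned, with exact confidence intervals.
4. State that a non-significant P value will not be taken as evidence of safety. At 30 per arm, power for a 0.5 SD effect on unadjusted change is only about 48%, so the interval must carry the conclusion.
5. If controls lack SSQ data, report the VR-arm change as uncontrolled and do not attribute it causally to VR.

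The cost is a change of wording, one model and one table. No new data are needed where control SSQ scores exist, and Trial status reports that data analysis had not been performed. The price is a less precise estimate than the within-arm mean change.
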